## **9.2 Populations for analysis**

### Intention to treat population

The intention to treat population (ITT) includes all patients randomised that received at least one dose of study medication and who have baseline data recorded.

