### **3. STUDY DESIGN**

This is a randomized controlled trial with three study groups. Children 6 to 59 months of age presenting at the OPD in Kaabong Hospital Kaabong district, Karamoja region and diagnosed with one or more of the three study diseases (malaria, diarrhoea and LRTI) are eligible for the study.

Children participating in this study will be randomised to one of the three groups to:

- A) Receive 14 days of RUTF supplementation with standard care and treatment or
- B) 14 days MNP supplementation with standard care and treatment
- C) Be included in a control group receiving standard care and treatment but not receiving nutritional supplementation (control group)

Individual follow-up will be 6 months. During this time, children in the RUTF or MNP group will receive 14 days nutritional supplement every time diagnosed with at least one of the three study diseases, not exceeding more than 14 days supplementation in any 28 day period.

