## **6.3 Treatment allocation**

The study dispenser\* will have access to a register with all unique study numbers and the assigned intervention. The study dispenser will allocate the study group to the participant when the participant collects the nutritional supplement. As such, the dispenser will be the only person of the study team to know the allocation scheme. The allocation register will be kept by the dispenser in such a manner that guarantees no unauthorized staff can have access. (see annex f9-dispensary allocation register)

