## **7.3 Control group**

For the purpose of this study, it is not practically feasible to design and manufacture a placebo for RUTF or the MNP. Children randomly assigned to the control group will receive equivalent care and follow-up as the children assigned to a study group receiving supplementation. The only difference is that they will not receive a nutritional supplement (current clinical practice does not include nutritional supplement).

---

\*One nurse assistant will be selected as study dispenser/treatment allocation (always will be the same person). The paragraph refers to randomization. It is only highlighting that no one except one individual will have access to the list in order to avoid anyone influencing the randomization of patients to treatment.

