## **8.5 Compliance**

Compliance regarding the consumption and acceptability of the nutritional supplements will be assessed only after the first 14 days of supplementation, through a questionnaire and collection of returned supplement sachets (used or unopened). The study dispenser will count and record the returned sachets (empty or unopened) after the questionnaire is completed.

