#### Baseline drop-out population

All patients enrolled who dropped out before the start of randomized treatment.

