#### **9.3.1 Primary analysis of the primary endpoint**

The primary endpoint is “negative nutritional outcome” of a child within the 6 months follow-up period as defined in section 8.8.1. The incidence rate (in formulae below referred to simply as ‘rate’) of “negative nutritional outcome” will be computed as the number of events divided by total observed person-time in each treatment group. As an “event” the first time a child reaches a negative nutritional outcome will be used. The primary analysis of the primary endpoint will be performed on the intention to treat population with no imputation of missing data.

In the primary analysis, RUTF will be compared to the control group.  
The hypotheses in this step are

$$\begin{aligned} H_0: \text{rate}_{\text{RUTF}} &= \text{rate}_{\text{Control}} \\ \text{vs.} \\ H_1: \text{rate}_{\text{RUTF}} &\neq \text{rate}_{\text{Control}} \end{aligned}$$

where  $\text{rate}_{\text{RUTF}}$  = rate of “negative nutritional outcome” in the children in the RUTF group, and  $\text{rate}_{\text{Control}}$  = rate of “negative nutritional outcome” in the children in the control group.

The comparison of rates among the treatment groups will be performed by a Poisson regression model, adjusted for nutritional status at enrolment (fixed effect) and will be performed within one model including the three intervention groups with contrasts for each two-group comparison. Tests will be two-sided with a significance level of 0.05.

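### The intention-to-treat set requires a dose of an undefined study medication, a condition the unsupplemented control arm cannot meet and which, if waived there, filters only the supplement arms

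*Protocol*

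**What the plan says.** Protocol section 9.2 sets three conditions for the ITT population. It "includes all patients randomised that received at least one dose of study medication and who have baseline data recorded". No definition of study medication is given and no exception is made for control. The per-protocol population is then drawn from the ITT population.

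Section 9.3.1 ties the primary test to this set: "The primary analysis of the primary endpoint will be performed on the intention to treat population with no imputation of missing data". That test compares RUTF with control.

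Section 3 describes the control group as standard care without supplementation. Section 7.3 explains that "it is not practically feasible to design and manufacture a placebo for RUTF or the MNP" and says of control children: "The only difference is that they will not receive a nutritional supplement".

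Three other places bear on how a dose would be established:
- Section 6.3, on allocation: "The study dispenser will allocate the study group to the participant when the participant collects the nutritional supplement".
- Section 8.5, on compliance: consumption "will be assessed only after the first 14 days of supplementation", by questionnaire and a count of returned sachets.
- Section 9.2, on a separate baseline drop-out population: "All patients enrolled who dropped out before the start of randomized treatment".

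**The concern.** The ITT definition is worded for a trial in which every arm is given a product. Here one of the two arms in the primary test is given none. The rule then has to be either left unapplied in control or reinterpreted, and the protocol does not say how.

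The obvious repair, keeping all control children and applying the condition to RUTF and MNP only, means that membership of the primary set depends on something that happens after randomisation in some arms and not in another. Section 6.2 states that participants are not blinded, so taking the supplement can depend on knowing the allocation and on how ill the child is. Section 1.3.1 names anorexia as the main cause of weight loss during infection. A child too anorexic to eat the supplement may therefore be at higher risk of the primary endpoint. Removing such children from the supplement arms alone would favour supplementation, and the comparison would no longer be between the groups as randomised.

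**Working it through.** **1. The plan's own figure.** For Poisson regression with a binary covariate (Signorini formula, assumed to be what the named software uses), with p = 0.5, rate ratio RR = 0.7, control rate 0.20, two-sided 0.05 and 80% power:

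N = [z(0.975)·√(1/(p(1−p))) + z(0.80)·√(1/(1−p) + 1/(p·RR))]² / (0.20·(ln RR)²) = [1.960·√4 + 0.8416·√4.857]² / (0.20 × 0.1272) ≈ 1311.

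Section 9.1 states 1320 (660 per group), which agrees; power at 1320 is 80.3%. Allowing for 10% drop-out, 660/0.9 = 733.3, hence 734 per group as stated. None of this depends on the ITT wording.

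**2. Applying the definition arm by arm.**
- RUTF and MNP: the condition can be met. Products are handed out on day 0 (section 6.3 and Table 1), and consumption is checked once, after the first 14 days (section 8.5).
- Control: no supplement and no placebo (sections 3 and 7.3), so there is no randomised product of which a dose could be received.
- Taken literally with study medication meaning supplement, 0 of 734 control children qualify and the primary rate ratio cannot be estimated.
- With the condition waived for control, it acts in RUTF and MNP only.

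**3. Which excluded children would matter.** Section 9.3.1 defines the rate as first events over observed person-time, without imputation. The first scheduled follow-up weight and MUAC are on day 14 and the final visit is on day 168 (Table 1). Suppose 5% of the RUTF arm (assumed) is lost by day 14 with no observed event:
- relative person-time with them: 0.95 + 0.05 × 14/168 = 0.954
- relative person-time without them: 0.95
- effect of excluding them: the RUTF rate rises by 0.954/0.95 − 1 ≈ 0.4%, so a ratio of 0.700 becomes about 0.703.

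That is negligible, and it goes against the supplement. A material effect needs children who took no supplement, stayed under observation and were excluded with their events.

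**4. Illustration of that case.** Assumptions, not from the protocol: no true effect; a share f of the supplement arm is excluded; those children have m times the average risk and full follow-up. The protocol supplies the control rate of 0.20 and about 660 evaluable children per arm.

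Spurious ratio = (1 − f·m)/(1 − f). For f = 0.10 and m = 2: (1 − 0.20)/0.90 = 0.889.

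For the type I error, SE = √(1/(n₁r₁) + 1/(660 × 0.20)), with n₁ = 734 × 0.9 × (1 − f) and r₁ = 0.20 × the spurious ratio. For f = 0.10 and m = 2: n₁ = 594.5, r₁ = 0.1778, SE = 0.1305, shift = |ln 0.889|/SE = 0.90, giving 14.7%.

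| Share excluded f | Risk multiple m | Spurious rate ratio | Two-sided type I error (nominal 5%) |
|---|---|---|---|
| 2% | 1.5 | 0.99 | 5.1% |
| 2% | 2 | 0.98 | 5.3% |
| 5% | 1.5 | 0.97 | 5.5% |
| 5% | 2 | 0.95 | 7.1% |
| 10% | 1.5 | 0.94 | 7.3% |
| 10% | 2 | 0.89 | 14.7% |

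If f = 0 the ratio is exactly 1. If the excluded children had below-average risk (m < 1), the ratio would exceed 1 and the bias would run against the supplement.

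**The case against.** The strongest reply is that the wording is loose but workable. Study medication might mean the drugs prescribed for malaria, diarrhoea or LRTI. The protocol usually calls RUTF and MNP supplements and keeps words such as drugs for disease treatment. Section 8.1 has the first dose of prescribed drugs taken in front of a study nurse, and Table 1 lists this on day 0 without distinction by arm. On that reading the condition is the same in all arms. Alternatively, received could simply mean dispensed, as it does in sections 7.1 and 7.2. Almost every supplement-arm child would then qualify on day 0, and a child who left before reaching the dispenser would have left before the allocation was disclosed.

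Part of this stands. The two outcomes in step 2 of the working are not the only possible ones, and under the dispensed reading very few children would be excluded. But the prescribed-drug reading is stated nowhere, and those drugs are standard care, not the randomised intervention. The dispensed reading still gives control nothing to receive. Section 8.5 governs compliance, not ITT membership, so it does not say that a child without a sachet count is to be dropped; nor does any other section say what would count as evidence of a dose.

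It may also be said that the analysis plan promised in section 9.3.5 would settle the term. The protocol does not leave this open, however. It fixes the primary population, so a plan that followed the definition would inherit the fault, and one that repaired it would depart from the protocol.

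**Conclusion.** The point holds as a wrongly stated rule for the primary analysis population. The dose condition cannot be applied to control on its natural reading, and waiving it for control alone creates a one-sided post-randomisation filter. Because the per-protocol set is built from the ITT set, the fault carries over to it.

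The size is unknown. It is near zero if few children are excluded, and the range of 0.99 to 0.89 for the spurious ratio rests entirely on the assumed share and risk of those excluded.

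Four stronger conclusions that a reader might draw are not supported:
- **That the control group would be empty.** Section 9.3.1 specifies RUTF against control on this very set, so control children are evidently meant to be in it.
- **That loss before day 14 would bias the result.** Such children add almost no events or person-time, as step 3 of the working shows.
- **That a particular bias can be predicted.** The protocol gives no figure for children who take no supplement, or for their risk.
- **That the baseline drop-out population is itself an error.** No analysis in section 9.3 uses it, and counting such children is ordinary participant-flow reporting. It would do harm only if used to remove randomised children from the ITT set.

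**What to change.** In section 9.2, define the ITT population as all randomised children with baseline data, analysed in the group assigned, regardless of supplement received or consumed. The baseline-data condition can stay because it applies equally to every arm.

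Keep any exposure condition for the per-protocol population, which already excludes children not treated according to their allocated group. The baseline drop-out population may remain for describing participant flow, with a statement that it does not remove randomised children from the ITT set.

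The cost is about one sentence plus that clarification. The sample size stays at 660 evaluable and 734 recruited per group. Power for the primary test is 80.3% with 1320 children, and would be 84.0% if all 2 × 734 = 1468 contributed full follow-up.

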### Per protocol Population

---

\* In Karamoja OCBA project, acute malnutrition is not treated (it is in charge of AAH) and we cannot estimate the duration of moderate acute malnutrition and the prevalence of malnutrition among sick children for calculating the sample size. The sample size calculation has been determined extrapolating data from MSF-OCA.

The per protocol population (PP) includes all patients of the ITT population which were treated following the specifications of the study protocol without major protocol deviations. Excluded from the per protocol population will be patients that meet at least one of the following criteria:

- Violation of one of the following exclusion criteria: exclusive breastfeeding, hospitalisation for serious complicated illness (e.g. chronic illness).
- Not treated according to the allocated intervention group
- Patient misses more than 2 monthly scheduled visits
- Patient misses 2 or more consecutive monthly scheduled visits
- Participation in other feeding programmes

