## **8.7 Withdrawal procedures**

Children will be withdrawn from the study if:

- i.) Participant fulfils criteria for acute malnutrition during follow-up period.
- ii.) There is a serious protocol violation
- iii.) Participant is erroneously included
- iv.) There is the risk that the nutritional supplement would negatively influence a prescribed medical protocol (i.e. medical treatment has priority).

Patients who become acute malnourished will be referred to MoH/Action Against Hunger (AAH) Supplementary and Therapeutic Feeding Program for care and treatment.

Participants who are withdrawn from the study will continue to be followed up if possible and monitored following standard study protocol. The use of data for analysis from withdrawn participants will be assessed by the study statistician.

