## **8.8 Endpoints**

### **8.8.1 Primary endpoint**

The primary endpoint is “negative nutritional outcome (NNO)” of a child within the 6 months follow-up period. The incidence of a negative nutritional outcome will be defined according to the baseline nutritional status.

- i) for children with no malnourishment at time of entry into study, “negative nutritional outcome” is defined as progression to moderate or severe malnourishment

Thus, the event of a child reaching a “negative nutritional outcome” at least once within 6 months of follow-up period will be compared between the three study groups.

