In addition, in case of significant and/or relevant differences of baseline values additional adjustment(s) for these factors will be performed within the model described above (in models with and without interaction), to address the potentially confounding or effect modifying effect of other variables. These variables include age (in months and binary: <36 months,  $\geq 36$  months), gender, breastfeeding practices, cough, underlying illnesses, socio-economic factors, food availability, length of illness before visiting MSF clinic, other health support sought during study, season during which child was in the study.

The amount and pattern of missing data of the primary endpoint will be checked by a person blinded to treatment allocation, and a decision based upon the result of this check will be made as to whether and how the imputation of missing primary endpoint data will be performed.

Additionally, the 6-months follow-up period will be split and analysed separately for 1 month periods with the method described above.

The analysis of the primary endpoints will also be repeated as described above separately for children with no malnourishment at time of entry into study and children with moderate malnourishment at time of entry into study.

The analysis of the primary endpoint will be repeated as described above for the per protocol population.

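### The per-protocol set excludes any child who joins another feeding programme, with no time limit, although every child who reaches the primary endpoint is referred to one, so the per-protocol repeat loses events in proportion to referral uptake.

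*Protocol*

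**What the plan says.** Four parts of the protocol bear on this.

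- **Endpoint (section 8.8.1).** For a child not malnourished at entry, the negative nutritional outcome "is defined as progression to moderate or severe malnourishment". Section 9.3.1 counts only the first such event per child.
- **What follows the endpoint (section 8.7).** One reason for withdrawal is "Participant fulfils criteria for acute malnutrition during follow-up period". Then: "Patients who become acute malnourished will be referred to MoH/Action Against Hunger (AAH) Supplementary and Therapeutic Feeding Program for care and treatment". Follow-up is meant to go on, but with a qualifier: "Participants who are withdrawn from the study will continue to be followed up if possible and monitored following standard study protocol".
- **Per-protocol population (section 9.2).** "Excluded from the per protocol population will be patients that meet at least one of the following criteria". The list includes "Participation in other feeding programmes" and two missed-visit criteria (more than two monthly visits missed, or two or more in a row). None of these is tied to the time before the event.
- **Use of that population (section 9.3.2).** "The analysis of the primary endpoint will be repeated as described above for the per protocol population".

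**The concern.** Read together, these sections make reaching the endpoint the start of a path that leads out of the per-protocol set. The child has the event, is referred, enrols, and by enrolling meets an exclusion criterion. The programme is clearly an outside one: the footnote to section 9.1 says that acute malnutrition is not treated in the sponsor's Karamoja project and is in the charge of AAH.

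The exclusion also serves no purpose for these children. Only the first event is counted, so feeding received afterwards cannot alter the counted outcome.

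At stake is a prespecified sensitivity analysis. It would have far fewer events than intended. If uptake differed between groups, it could contradict or flatter the intention-to-treat result for reasons unrelated to supplementation. The missed-visit criteria could remove further event children, because visits after withdrawal are kept up only where possible.

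**Working it through.** **Inputs from the protocol (section 9.1).** Control rate 0.20 and RUTF rate 0.14 per 6 months; 660 children per group after dropout; 80% power; 0.05 level, two-sided by section 9.3.1.

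**Input not in the protocol.** Uptake of the referral, written u. It is assumed and varied.

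**The plan's own figure.** For Poisson regression with a binary covariate and equal allocation,

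N = (1.96·√V0 + 0.842·√V1)² / (0.20·(ln 0.7)²), with V0 = 1/(0.5·0.5) = 4 and V1 = 1/0.5 + 1/(0.5·0.7) = 4.857.

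This gives N = 1311 against the stated 1320, and power of 80.3% at 1320. Dropout: 660/0.90 = 733.3, rounded up to 734. The sample size reproduces and is not in question.

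**Expected first events.**

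- Control: 660 × (1 − e^−0.20) = 119.6, about 120.
- RUTF: 660 × (1 − e^−0.14) = 86.2, about 86.
- Undistorted per-child ratio: 86.2/119.6 = 0.72. This is the comparator below. It differs from the rate ratio of 0.70 because it is on the per-child scale.

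**Per-protocol set under the rule as written.** Events kept = events × (1 − u). Children kept = 660 − events × u. Other exclusions are ignored.

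| Uptake, control / RUTF | Events kept, control / RUTF | Children kept, control / RUTF | Per-child ratio |
|---|---|---|---|
| 0% / 0% | 119.6 / 86.2 | 660 / 660 | 0.72 |
| 50% / 50% | 59.8 / 43.1 | 600 / 617 | 0.70 |
| 80% / 80% | 23.9 / 17.2 | 564 / 591 | 0.69 |
| 80% / 70% | 23.9 / 25.9 | 564 / 600 | 1.02 |
| 80% / 90% | 23.9 / 8.6 | 564 / 582 | 0.35 |
| 100% / 100% | 0 / 0 | 540 / 574 | not estimable |

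Example for 80% / 70%: (25.9/600) / (23.9/564) = 1.02.

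**Precision at equal uptake.** The standard error of the log ratio is roughly √(1/events control + 1/events RUTF). With no loss it is √(1/119.6 + 1/86.2) = 0.14; at 80% uptake it is √(1/23.9 + 1/17.2) = 0.32, more than twice as large.

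**Sensitivity to reading the rates as proportions.** The expected events are then 660 × 0.20 = 132 and 660 × 0.14 = 92.4, and 80% uptake leaves 26.4 v 18.5. The conclusion is the same.

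**The case against.** The strongest reply is that section 9.2 first describes the per-protocol population as children without major deviations. A referral that the protocol itself orders, after the event has been counted, is not naturally a deviation. On that view the criterion was meant for feeding alongside the study supplement that would confound the comparison, and the planned analysis plan (section 9.3.5) could settle the time window. This is a sensible guess at the intent. It does not remove the problem, because section 9.2 lists participation itself as a ground for exclusion, says that any one criterion is enough, and makes no exception. The criteria are fixed in the protocol, not left open.

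Other parts of the reply stand, and they limit the point. A reader might infer each of the following, and the protocol does not support it:

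- *The trial's main result is compromised.* The primary analysis is by intention to treat (section 9.3.1). Only the per-protocol repeat is touched.
- *Every event is deleted.* Section 8.7 orders referral, not enrolment. All events go only at complete uptake.
- *The per-protocol analysis would compare referral uptake instead of malnutrition.* At equal uptake the ratio barely moves. Serious bias needs unequal uptake. Guardians are not blinded, so this is possible, but clinical staff are blinded (section 6.2) and nothing in the protocol shows that it would happen.
- *The non-inferiority step is undermined.* Section 9.1 calls that hypothesis explorative, and no section gives the per-protocol set a special role in it.
- *The 6-month secondary endpoints lose the sickest children.* Section 8.7 says "The use of data for analysis from withdrawn participants will be assessed by the study statistician". That leaves the question open; it does not say that data after the event are dropped. Section 6.2 lists statisticians among the blinded staff, and section 9.3.3 treats secondary p-values as explorative.

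**Conclusion.** The point holds for the per-protocol repeat of the primary analysis. Followed as written, the exclusion in section 9.2 and the referral in section 8.7 delete counted first events in proportion to uptake, and no part of the protocol reconciles them.

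The size depends wholly on uptake, which is assumed. With equal uptake the harm is lost precision: about 41 events in place of about 206 at 80%. A difference of 10 percentage points between groups at that level moves the per-child ratio from 0.72 to about 1.02 or about 0.35, depending on its direction. These figures rest on the planned rates, on 660 children per group, and on no other per-protocol exclusions. Any loss through the missed-visit criteria would come on top; it cannot be sized from the protocol.

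**What to change.** In section 9.2, apply the feeding-programme criterion and both missed-visit criteria only to the time before the first NNO. State that a child who reaches NNO before any such deviation stays in the per-protocol population with the event counted. Sections 8.7 and 9.2 must be reconciled in this way for the analysis; no change to referral, withdrawal or supplementation is proposed.

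The cost is a few lines of text and one data item: the date of joining a feeding programme must be available relative to the date of the NNO. The protocol text does not say that this date is recorded, so the follow-up form should be checked for it. With the change, the per-protocol analysis keeps up to the roughly 120 v 86 expected first events, less those of children excluded for deviations before the event.
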